### Adverse event reporting and harms {22}

All (serious) adverse events ((S)AEs) related to study reported by surgeons or participants will be recorded. Participants in both groups will be asked in standardized manner (7–10 days, 3 months and 12 months post-op). If any major event occurs between inspections, each participant will have the opportunity to contact the Study Director or Study Secretary.

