### Intervention description {11a}

As M3 hernias are difficult to diagnose before the surgery, all patients scheduled for laparoendoscopic repairs will be asked to participate. After the dissection, reduction of hernia sack, and creation of preperitoneal space, the surgeon will open a sealed envelope and find out what technique he/she will have to perform and participants will be randomly allocated to one arm of the study. Dissection of preperitoneal space and placing the mesh in the groin area are considered to be the most important stage of the procedure—every surgeon will have to take visual record of that part of surgery to make sure proper technique was applied. Patients will not be aware of the method used during surgery. When using fixation material with histoacryl glue, it will be placed in previously predefined places (Fig. 2). Before recruiting patients, a 2-day “bootcamp” meeting was scheduled. Each center designated one surgeon responsible for conducting the trial in their hospital and sent him/her to attend the meeting. The meeting consisted of lectures on the first day and exhibition surgeries performed by experts on the second day. A meeting took place to unify the surgery technique and make sure every center will follow the same protocol. After operation, surgeon will fill the study form and put it in a sealed envelope. All patients in both arms will be given standard recommendation to avoid intensive physical activity for 2 weeks post-op. Standard wound care will be explained to patients in both groups.

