#### Secondary outcomes

Besides primary outcome secondary outcomes will also be noted.

1. Pain sensation assessed with Visual Analog Scale measured during hospital stay, 7 days post-op, 3 months, and 12 months after surgery.

2. Incidence of other complications (seroma, hematoma, infections) assessed during hospital stay, 7 days post-op, 3 months, and 12-months after surgery.

7 day post-op visit will be performed by a surgeon blinded to the arm allocation. During the visit, another form will be filled and placed in encoded envelope. Three months post-op and 1-year post-op follow-up, a phone call will be performed by the Study Secretary blinded to the allocation. Telephone call after inguinal hernia surgery is a verified and validated form of follow-up [5, 6]. If there are any concerns, the patient will be asked to attend an outpatient appointment.

Participant demographics including general medical history, body mass index, co-morbidities, age, sex, smoking status, history of hernia repairs, and family history of hernias will be noted and placed in sealed coded envelopes.

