## Assignment of interventions: blinding

### Who will be blinded {17a}

Trial participants and Study Secretary performing phone call follow-up visit will be blinded to the method used. Surgeon will be blinded for as long as possible (after the dissection, reduction of hernia sack, and creation of preperitoneal space are achieved).

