## Discussion

In our opinion, flat, macroporous implants used in most laparoendoscopic inguinal hernia repairs performed in Germany (included in the Herniamed Database) are not the most appropriate for this type of procedure. While the groin operated from the anterior approach (Lichtenstein’s operation) is approximately a flat structure and thus flat implants are appropriate in this case, laparoendoscopic procedures differ in their specificity. The groin seen from behind is by no means a flat structure. Curvatures of pubic bones, iliac vessels, etc., require an appropriate implant that matches its shape. This will enable, e.g., obtaining many contact points, which in turn, by creating friction, keep the implant in its initial position. The above issues are of little importance in the case of small hernia defects. Small size of the gate (< 3 cm) does not allow the implant to move. However, in the case of large simple and complex hernias, the type of implant is a key issue, and the mere presence of such defects is a risk factor for recurrence.

In the study by Zamkowski et al., rigid spatial implants (3d Max, Dextile Anatomical Mesh, Filaprop 3d Mesh) did not change their position regardless of the increase in intra-abdominal pressure. Thus, they did not give rise to a rapid recurrence [3]. In the case of flat, macroporous implants, similar mechanical stability can only be achieved by using fixing materials, as shown by the analysis of Mayer et al. [2]. It is worth mentioning that the mesh mounting itself may involve a number of potential complications.

In addition to the obvious ones, which include the increase in the cost of the procedure and longer duration of the surgical procedure, there are many others. The literature describes the possibility of migration of the fixation with meshoma formation, adhesions, chronic postoperative pain, and infections. Each fixation itself carries a risk of damage to the surrounding tissues, including accidental nerve damage. This applies in particular to fixation with sutures, takers, or staples and has been proven in post-mortem studies [7, 8]. Finding a way to avoid the need for fixation by using dedicated implants will eliminate all of the above potential risks [1, 9–12].

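### The adverse event rule records only events considered related to the study and names no judge of relatedness, so unlisted events around the operation could be recorded differently by arm or not at all

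*Protocol article*

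**What the plan says.** Four parts of the protocol article bear on this point.

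- **Recording rule.** Adverse event reporting and harms {22}: "All (serious) adverse events ((S)AEs) related to study reported by surgeons or participants will be recorded". The same section says that both arms are questioned by a standard procedure at 7–10 days, 3 months and 12 months. Participants can contact the Study Director or Study Secretary about a major event in between.
- **Who knows the arm.** Who will be blinded {17a}: "Trial participants and Study Secretary performing phone call follow-up visit will be blinded to the method used". For the operator the promise is weaker: "Surgeon will be blinded for as long as possible", which means until the preperitoneal space has been created. Intervention description {11a} adds: "After operation, surgeon will fill the study form and put it in a sealed envelope". By then the allocation envelope has been opened.
- **Outcomes collected in any case.** Secondary outcomes lists pain on a visual analog scale, and seroma, hematoma and infection, during the hospital stay, at 7 days, 3 months and 12 months. No relatedness condition is attached. On the first visit: "7 day post-op visit will be performed by a surgeon blinded to the arm allocation". The later calls are made by the blinded Study Secretary.
- **Expected harms.** The Discussion attributes to fixation "migration of the fixation with meshoma formation, adhesions, chronic postoperative pain, and infections" and presents avoiding fixation as the way to remove such risks. It names no harm specific to the anatomical mesh.

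**The concern.** A rule that records an event only if it is considered related places a judgement before the data. An event judged unrelated need leave no trace, so nobody can later reclassify it, count it or compare it between arms. If the person applying the filter knows the arm and expects harm mainly from one technique, the same event may pass in one arm and be dropped in the other.

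The primary question is recurrence, and this rule does not touch it. At stake is the general safety record. The arms differ in mesh type and weight as well as in fixation, so an unexpected harm of either mesh is the kind of event that an early view on causation can miss. The Data Monitoring and Ethics Committee, which the article charges with participant safety, might see only the filtered record.

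**Working it through.** The article gives no figure on this point: no expected adverse event rate and no attribution rate. The check is therefore a reading of the sections against each other.

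1. **Is relatedness a condition?** Yes, as section {22} is worded. It qualifies which events are recorded, and it covers serious and non-serious events alike.

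2. **Who judges relatedness?** Not stated. Section {22} names surgeons and participants as the sources of reports. Reporting an event and judging its cause are different tasks, and the article assigns only the first.

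3. **Which reporters can know the arm?**

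| Period | Who collects or reports | Knows the arm? |
|---|---|---|
| Operation, after the envelope is opened | Operating surgeon, who completes the form | Yes |
| Hospital stay | No blinded assessor named | Possible |
| 7–10 day visit | Surgeon | No, stated as blinded |
| 3- and 12-month calls | Study Secretary | No, stated as blinded |
| Between contacts | Participant, to Study Director or Study Secretary | Participant and Secretary stated as blinded; Director not stated |

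4. **Which events depend on the filter?** Pain, seroma, hematoma and infection do not, because they are outcomes at every time point. Two of the harms listed in the Discussion, chronic pain and infection, are therefore captured whatever anyone thinks of their cause. The events that depend on section {22} alone are the unlisted ones, such as visceral injury, bowel obstruction or reoperation.

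5. **Where do steps 3 and 4 overlap?** In unlisted events during the operation and hospital stay. There the reporter may know the arm and no other route into the record is described. Later unlisted events still meet the relatedness condition, but through sources that are mostly stated to be blinded. They are more likely to be lost equally in both arms than selectively in one.

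6. **Can the bias be sized?** Let *p* be a true rate of such events, equal in both arms, and let *a*F and *a*N be the proportions considered related under fixation and non-fixation. The recorded rates are *p* × *a*F and *p* × *a*N, and the apparent ratio of non-fixation to fixation is *a*N / *a*F. The ratio is 1 if attribution does not depend on the arm and falls below 1 if events are attributed more readily under fixation. The article gives none of *p*, *a*F or *a*N, even approximately, so no value follows from it.

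**The case against.** The strongest reply has four parts.

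- **Who decides.** A reader might infer that the operating surgeon decides relatedness. The article does not say so, and the causality procedure may well stand in the full protocol. This stands: the surgeon's role as judge is not established. The recording condition, however, is stated in the article, so it is not merely a detail left out. The phrase may have been meant loosely, for any event arising during participation; if so, clearer wording costs nothing.
- **The scope.** A reader might infer that the whole safety comparison passes through an unblinded opinion. The documents do not support that. The named complications and pain carry no relatedness condition, participants are blinded, questioning is standardized, and assessors from the first visit on are described as blinded. This stands and confines the point to unlisted events, chiefly peri-operative ones.
- **The direction.** The Discussion speaks of fixation in general and links tissue and nerve injury above all to sutures, tackers and staples. It does not mention migration of glue, and it describes the glue used in the control arm as atraumatic. Surgeons may thus expect less harm in this control arm than the list of fixation risks suggests. This stands: a tilt towards the non-fixation arm is plausible but not shown.
- **The importance.** The objective concerns recurrence, and the article announces no formal comparison of general adverse events between arms. This also stands and limits the severity. It does not remove the value of a complete record for the safety committee.

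**Conclusion.** The point holds in a limited form. Section {22} makes relatedness a condition for recording adverse and serious adverse events and names no judge, blinded or otherwise. The exposure is confined to events outside the listed outcomes, chiefly during the operation and the hospital stay, where the reporting surgeon knows the arm. Such events could be recorded differently by arm, or be lost to the Data Monitoring and Ethics Committee.

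No size can be given: a claim that attribution alone would yield a particular apparent reduction in harms would rest on invented rates. The primary analysis of recurrence is unaffected.

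The conclusion assumes that the recording rule is applied as written and that the 7-day surgeon and the Study Secretary are in fact blinded, as the article says. Severity is minor; this is a cheap improvement.

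**What to change.** Reword Adverse event reporting and harms {22} along these lines: all adverse and serious adverse events from surgery to 12 months are recorded in both arms, whatever their judged relation to the study. Enter relatedness in a separate field, say who completes it, and have it judged without knowledge of the arm where possible. Tabulate all events by arm, with related events as a subset, and give that full table to the Data Monitoring and Ethics Committee.

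The cost is a few more entries on the operative form and at the contacts already planned at 7–10 days, 3 months and 12 months. No visit, participant or test is added. The change is best made early, because events that were not recorded may not be recoverable later.

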### Frequency and plans for auditing trial conduct {23}

The Project Management Group will play a vital role in the daily operations and oversight of the trial. To ensure smooth execution and address any potential challenges promptly, the Project Management Group will meet biweekly. During these meetings, trial conduct will be reviewed, potential issues will be discussed, and resolutions will be sought. The Trial Steering Group will provide strategic direction and oversight to the trial and will convene on a quarterly basis, or more frequently if required by specific circumstances. Meetings will involve reviewing trial conduct, evaluating milestones achieved, and offering guidance on upcoming phases of the trial.

### Plans for communicating important protocol amendments to relevant parties (e.g., trial participants, ethical committees) {25}

Any modifications made to the protocol after its original acceptance will be submitted to Bioethics Committee in District Health Center in Gdańsk and have to be approved by the Steering Committee and Collaborators. Modification and new information will be communicated to the included participants.

### Dissemination plans {31a}

The study investigators will inform all participants about the results of the study. The results of the study will be reported in peer-reviewed international journals and popular science articles and presented at local and international conferences. Policymakers, healthcare providers, funding bodies, and other important stakeholders, e.g., patient organizations, will be informed on the outcomes of the MEFI Trial.

### Patient Public Involvement (PPI)

The outcomes of this research should be accessible and understandable to patients as well. Project Management Group will be collaborating with patient representatives to develop a patient-friendly summary of trial’s finding. This summary will be made available on our website and will be shared with patient support groups and relevant organizations. Also, there will be a feedback mechanism wherein participants can share their experience of being part of the trial. This feedback will be periodically reviewed Project Management Group and the patient advisory group to identify areas of improvement and implement necessary changes.

## Discussion

In our opinion, flat, macroporous implants used in most laparoendoscopic inguinal hernia repairs performed in Germany (included in the Herniamed Database) are not the most appropriate for this type of procedure. While the groin operated from the anterior approach (Lichtenstein’s operation) is approximately a flat structure and thus flat implants are appropriate in this case, laparoendoscopic procedures differ in their specificity. The groin seen from behind is by no means a flat structure. Curvatures of pubic bones, iliac vessels, etc., require an appropriate implant that matches its shape. This will enable, e.g., obtaining many contact points, which in turn, by creating friction, keep the implant in its initial position. The above issues are of little importance in the case of small hernia defects. Small size of the gate (< 3 cm) does not allow the implant to move. However, in the case of large simple and complex hernias, the type of implant is a key issue, and the mere presence of such defects is a risk factor for recurrence.

In the study by Zamkowski et al., rigid spatial implants (3d Max, Dextile Anatomical Mesh, Filaprop 3d Mesh) did not change their position regardless of the increase in intra-abdominal pressure. Thus, they did not give rise to a rapid recurrence [3]. In the case of flat, macroporous implants, similar mechanical stability can only be achieved by using fixing materials, as shown by the analysis of Mayer et al. [2]. It is worth mentioning that the mesh mounting itself may involve a number of potential complications.

In addition to the obvious ones, which include the increase in the cost of the procedure and longer duration of the surgical procedure, there are many others. The literature describes the possibility of migration of the fixation with meshoma formation, adhesions, chronic postoperative pain, and infections. Each fixation itself carries a risk of damage to the surrounding tissues, including accidental nerve damage. This applies in particular to fixation with sutures, takers, or staples and has been proven in post-mortem studies [7, 8]. Finding a way to avoid the need for fixation by using dedicated implants will eliminate all of the above potential risks [1, 9–12].

Implants in the control group in our study are fixed atraumatically, using tissue glue. The weak recommendation contained in the guidelines for the treatment of hernias states that atraumatic fixation (with the use of fibrin or acrylic glue) reduces the risk of damage to the surrounding tissues [1]. There is also the issue of cost-effectiveness behind this solution—adhesives are potentially the cheapest method of fixing. Considering the above, in our study, in the control group, we adopted this method of implant attachment.

A trend is slowly emerging in the literature to use heavier implants in the case of large and complex inguinal defects treated with laparoendoscopic techniques. Some studies point to the superiority of heavier implants in the context of recurrence, especially when routine fixation is not used [13, 14]. Previously mentioned analysis of Swedish Hernia Registry showed that M3 hernia repairs are not connected with higher recurrence rate as long as larger, heavier mesh is used [4].

However, the final confirmation of the above in the conditions of a randomized clinical trial is still missing.

Confirmation in the RCT that the recurrence rate for spatial implants in M3 hernias is the same as for fixation of flat implants will be the last element necessary to apply for a change, or at least a supplement, to the international guidelines.

## Trial status

Protocol version number and date: version 2.0 date 19/01/2023. Recruitment for the trial began in February 2023 and is expected to be completed by February–March 2024.

## Data Availability

The datasets used during the current study are available from the corresponding author on reasonable request.

## Abbreviations

TAPP: Trans-abdominal preperitoneal
TEP: Totally extraperitoneal
EHS: European Hernia Society
VAS: Visual Analog Scale
ANOVA: Analysis of Variance
StPPM: Standard Pure Polypropylene Mesh
RCT: Randomized controlled trial
SAE: Serious adverse events
PPP: Preoperative progressive pneumoperitoneum
ACS: Abdominal compartment syndrome
